## Abstract

**Background:**

Pulmonary arterial hypertension (PAH) is a progressive, chronic disease without curative treatment. Large registry data of these patient populations have been published, although, phenotypic variants within each subtype of PAH have not been elucidated. As interest towards personalized medicine grows, the need for a PAH cohort with a comprehensive understanding of patient phenotypes through multiomics approaches, called deep phenotyping, is on the rise. The PAH Platform for Deep Phenotyping in Korean Subjects (PHOENIKS) cohort is designed to collect clinical data as well as biological specimens for deep phenotyping in patients with idiopathic PAH (IPAH) and heritable PAH (HPAH) in Korea.

**Methods:**

A total of 17 regional hospitals are currently working on enrolling up to 100 consecutive IPAH/HPAH patients for obtaining clinical data and biological specimens across Korea. The diagnosis of PAH is based on right heart catheterization. All clinical data is stored in a government-based online database. Each participating hospitals collect a whole blood sample from each patient, through which DNA, RNA, serum, plasma, and peripheral blood mononuclear cells will be extracted from the buffy coat layer for further multiomics analysis.

**Results:**

Not applicable.

**Conclusions:**

The PHOENIKS cohort is enrolling IPAH and HPAH patients across Korea to determine the prognosis and drug response in different phenotypic variant. The data generated by this cohort are expected to open new doors for personalized medicine in PAH patients of South Korea.

**Trial registration:**

ClinicalTrials.gov NCT03933579. Registered on May 1st, 2019.

## Introduction

Pulmonary hypertension (PH) is defined as a mean pulmonary artery pressure ≥ 25 mmHg, while pulmonary arterial hypertension (PAH) is one of the five categories of PH classified by World Health Organization (WHO) [1]. PAH is precapillary pulmonary hypertension caused by vasoconstriction and proliferative remodeling of precapillary arteries resulting in increased pulmonary vascular resistance, right ventricular heart failure, and eventually, death [2]. Although previously published large scaled registries have substantially improved our understanding of PAH [3–6], these data lack deep phenotyping, which is, gathering the detailed genetic and molecular information that underlies the prognosis or response to specific drugs of each patient [7–12]. Current registries, such as the National Biological Sample and Data Repository for PAH and the Biomedical Research Identification of Genetic Etiology of PAH (BRIDGE-PAH), are actively recruiting patients in the US and UK, respectively, and are aiming for deep phenotyping of PAH patients [12, 13]. These trends give rise to the need for an East Asian population-based PAH registry that incorporates deep phenotyping as well as robust genetic and multiomics level data from PAH patients. The PAH Platform for Deep Phenotyping in Korean Subjects (PHOENIKS) cohort aims to build a database based on clinical data and biospecimens for PAH patients across South Korea.

## Methods

### Study objectives

The current study is a multicenter registry and biobank enrolling South Korean populations to construct a database for the elucidation of molecular and genetic modifiers of PAH. The main goal of the current study is to evaluate clinical outcomes in South Korean PAH subjects and collect biospecimens for subsequent deep phenotypic studies. Detailed study objectives are shown in Table 1. Specific goals regarding deep phenotyping will be described in subsequent studies.

**Table 1 Tab1:** Study objectives of the cohort

Study Objectives	
1. To build a robust IPAH and HPAH patient registry through collaborative network across South Korea with 16 regional hospitals across the country.	
2. To perform a long-term follow up of registered patients to characterize the clinical course of IPAH and HPAH patients among South Koreans.	
3. To collect biospecimens of enrolled patients and to build a biobank for Korean PAH and HPAH.	
4. To identify novel genetic mutations via next generation sequencing of the collected biospecimens.	
5. To deep-phenotype PAH and HPAH through a detailed omics-level study from a large collection of patient samples.	

*IPAH* idiopathic pulmonary arterial hypertension, *HPAH* hereditary pulmonary arterial hypertension

### Study sample

The current study will initially exclude the most frequent form of PAH in South Korea, i.e., connective tissue disease (CTD)-related PAH [5], and focus on the diagnosis and deep phenotyping of idiopathic PAH (IPAH) and heritable PAH (HPAH) patients. The enrolling 17 tertiary centers within South Korea are as follows - Gachon University Gil Medical Center, Incheon; Sejong General Hospital, Bucheon; Chonnam University Hospital, Gwangju; Keimyung University Dongsan Medical Center, Daegu; The Catholic University of Korea St. Vincent’s Hospital, Suwon; Seoul National University, Seoul; Chungnam National University Hospital, Daejeon; Wonju Severance Christian Hospital, Wonju; Asan Medical Center, Seoul; Wonkwang University Hospital, Iksan; Chungbuk National University Hospital, Cheongju; Yonsei University Severance Hospital, Seoul; The Catholic University of Korea Seoul St. Mary’s Hospital, Seoul; Seoul National University Bundang Hospital, Bundang; Pusan National University Hospital, Pusan; Chonbuk National University Hospital, Jeongju; Pusan National University Yangsan Hospital, Yangsan. Patients are being enrolled through January 1st, 2018 and December 31st 2021. The inclusion criteria are as follows: (1) over 18 years of age, (2) mean pulmonary arterial pressure of 25 mmHg or higher confirmed by right heart catheterization (RHC), (3) pulmonary vascular resistance ≥240 dynes∙s∙cm^− 5^, and (4) left ventricle diastolic pressure (LVDEP) or pulmonary capillary wedge pressure (PCWP) ≤ 15 mmHg. Exclusion criteria are: (1) patients with drug-induced-PAH; (2) CTD, human immunodeficiency virus (HIV) infection, portal hypertension, congenital heart disease, or schistosomiasis-associated-PAH; (3) long-term responders to calcium channel blockers; and (4) PAH patients with overt features of venous capillary involvement, leaving IPAH and HPAH patients among group 1 of PH to be evaluated [14]. HPAH will be diagnosed by identifying patients with heterozygous pathogenic variants of predetermined genes such as *BMPR2, ACVRL1, ENG, CAV1, SMAD1, SMAD4, SMAD9, KCNK3,* and *EIF2AK4.* Patients without a specific genetic mutations will then be categorized as IPAH patients. The genomic data of family members across 3 pedigrees of an HPAH patient will also be analyzed. All clinical and biological data will be reported to a customized web-based case report form called the iCReaT system managed by the Korean Center for Disease Control. Although the current analysis is planned to be limited to IPAH and HPAH patients, our steering committee plans to expand to all types of PAH in subsequent studies. Among the estimated 1500 total patients of PAH in South Korea, our goal is to enroll 100 consecutive patients.

### Baseline data, clinical outcomes, and biospecimen collection

The baseline data from the registered patients across the 17 regional hospitals will include the following: WHO functional classification, 6-min walking tests, blood samples, electrocardiograms, chest X-rays, echocardiography, optional pulmonary-cardio exercise tests, optional cardiac MRI, RHC, and the evaluation of comorbidities. Detailed information for each exam is displayed in Table 2. The registered patient will be followed up on a regular basis for further data and biospecimen collection. Mortality and hospitalization is planned to be tracked for clinical outcomes.

**Table 2 Tab2:** Clinical data entries of the cohort

Parameter	Specific categories
Identification Data	Patient code, Date of birth, Registered date
	Sex, Postal code, Height & Weight
Onset	Year of first symptom/first hospital visit/PAH diagnosis
WHO functional class at diagnosis	Class I-IV
Symptoms at diagnosis	Dyspnea/Chest pain/
	Syncope/Edema/Palpitation/Weakness/Other(specify)
Signs at diagnosis	Cardiac murmur/Hepatomegaly/Elevated JVP/Pitting edema/Ascites
Vital sign at diagnosis	Blood pressure-Heart rate-Respiratory rate-Body temperature
PAH family history	Y/N, Specify
Medical history	Connective tissue disease, Congenital heart disease
	PAH inducing drug history, HIV diagnosis/treatment history, Chronic hepatic disease
6MWT	Distance (meters), Blood pressure (before & after),
	Pulse rate, O_2_ Saturation
Blood Chemistry and Hemodynamics	NT-proBNP, troponin I, PT, Cr,
Electrocardiogram	Normal, RVH, nonspecific
Imaging studies	Chest radiography, Echocardiography, Computed chest tomography, Cardiac MRI
Cardiopulmonary exercise test	pCO2, VE/VCO_2_, VO_2_/HR, peak VO_2_
RHC	Systolic, diastolic, mean pulmonary arterial pressure, pulmonary wedge pressure, right heart pressure, central vein, S_v_O_2%,_ Pulmonary vascular resistance

*PAH* pulmonary arterial hypertension, *HIV* human immunodeficiency virus, *6MWT* 6-min walk test, *NT-proBNP* N-terminal prohormone of brain natriuretic peptide, *PT* prothrombin time, *Cr* creatinine, *RVH* right ventricular hypertrophy, *MRI* magnetic resonance imaging, *RHC* right heart catheterization

With the patient’s blood sample, DNA, RNA, serum, plasma, and peripheral blood mononuclear cells (PBMC) from the buffy coat will be separated and be extracted for further storage and studies. For the DNA sample, 2.5 ml whole blood will be stored in a DNA tube (PAXgene® Blood DNA Tube, BD Science, San Jose, CA) at each enrolling center, and it will be transported to the main center at 4–10 °C. At the main center, it will then be transferred to a 2-ml cryotube to be stored at − 70–80 °C. For RNA collection, 2.5 mL whole blood will be collected in PAX gene RNA tubes, and will be sent to the main center at 4–10 °C, where it will also be further transferred to a cryotube to be stored at − 70–80 °C.

Serum, plasma and the buffy coat will also be collected. At the respective collection sites, serum will be collected in serum separation tubes, and 30 min after venipuncture, it will be centrifuged and stored at − 20 °C. For plasma, cell preparation tubes will be used within 2 h of blood collection. Then, each sample will be ready to be stored at − 20 °C by treating the samples with human serum type antibody, DMSO, and freezing medium. To separate and extract PBMC, the white buffy coat layer will be separated and be stored in a 1.5-ml tube with freezing medium at − 20 °C. The collected baseline data will then go through a clean-up process and further evaluation of its quality will be done. In addition, five patients will be selected to perform whole-genome sequencing. Half the sample of all collected biospecimens will be stored at the Korean National Institute of Health main storage and the other half at Gachon Cardiovascular Research Institute at Gachon University. Biospecimens will be further used for multiomics studies and subsequently deep phenotyping. Specific methods regarding multiomics deep phenotyping is beyond the scope of this paper and will be dealt with in the subsequent study.

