## Discussion

A high degree of phenotypic variability within IPAH and HPAH has been increasingly recognized, bringing into question the efficacy of the current PAH treatment that uniformly targets the classical PAH pathways [15, 16]. Such heterogeneity has resulted in variable treatment responses among patients. Accordingly, it is necessary to develop better methods for personalized medicine - predicting responses of different classes of PAH medications in each individual. Although, personalized medicine is a familiar concept that is already used in PAH, as patients with vasoreactivity with nitric oxide are treated with calcium channel blockers, better understandings of the response to treatment in different cellular and molecular backgrounds is necessary for a more precise prediction [8]. Deep phenotyping is a multiomics approach to understand the cellular and molecular processes that underlie the variability to each treatment. Using a multiomics approach allows the acquisition of large amounts of data from gene sequencing and proeomic analysis to metabolic profiling [7]. Accordingly, personalized medicine can be achieved only through the foundation of deep phenotyping. Through such data, the mechanisms underlying the phenotypic variability in treatments or type of PAH may be understood [9, 10, 17–20]. We expect that the large datasets collected by the PHOENIKS project will cover many novel molecular-level mechanisms that may explain the heterogeneous phenotypes among South Korean individuals.

Previous registries in Europe, North America and Asia have focused on the clinical aspects of the disease [3–6, 21], providing better understandings of the prevalence of each PAH subtype and prognosis. Such data, however, were not designed to elucidate the gaps in our understandings of deep phenotyping [22]. The aims of the PHOENIKS cohort share similarities with those of the new BRIDGE-PAH registry in the UK and the National Biological Sample and Data Repository for PAH in the US [12, 13]. Both studies are currently actively recruiting patients and are expected to elucidate the molecular pathobiology of PAH by a multiomics approach. To our knowledge, the PHOENIKS cohort will be the first PAH registry acquiring deep phenotypic data in all of Asia.

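### As written, the article's plasma instruction adds a cell-freezing mixture to plasma banked for multiomics; limit that step to the PBMC tube and state the repository temperature

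*Protocol article*

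**What the plan says.** All of the handling text is in the Protocol article, Methods, Baseline data, clinical outcomes, and biospecimen collection.

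- **Plasma.** "For plasma, cell preparation tubes will be used within" 2 h of blood collection. The next sentence has each sample made ready for −20 °C storage "by treating the samples with human serum type antibody, DMSO, and freezing medium".
- **PBMC.** A separate sentence follows: "the white buffy coat layer will be separated and be stored in a 1.5-ml tube with freezing medium at" −20 °C.
- **Serum.** At the collection sites, 30 minutes after venipuncture, "it will be centrifuged and stored at" −20 °C.
- **DNA and RNA.** Both travel to the main center at 4–10 °C. For RNA the text continues: "where it will also be further transferred to a cryotube to be stored at" −70 to −80 °C. DNA is stored at the same temperature.
- **Destination.** "Half the sample of all collected biospecimens will be stored at the Korean National Institute of Health main storage", and the other half at the Gachon institute. No temperature is given there for serum, plasma or PBMC.
- **Use.** "Biospecimens will be further used for multiomics studies and subsequently deep phenotyping". The Discussion says that a multiomics approach allows "the acquisition of large amounts of data from gene sequencing and proeomic analysis to metabolic profiling", and the Conclusion names protein translation and metabolites among the things to be related to drug response and prognosis.

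**The concern.** DMSO and freezing medium are additives for preserving cells, and plasma is the cell-free fraction. A site that follows the sentences in order would mix a solvent, a freezing medium and a human-derived product into the patient's plasma before freezing it. Protein or metabolite measurements on that aliquot would then partly reflect the additive, and the mixture cannot be separated again afterwards.

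This bears on the study's central purpose. Study objectives makes biospecimen collection for deep phenotyping part of the main goal, and Table 1 lists an omics-level study of the samples. There are 17 centers. If some treat plasma literally and others read the step as meant for cells, the specimens will differ by center in a way that no later analysis can remove without knowing who did what.

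The second, smaller concern is that three of the five specimen types have only the warmer temperature stated, and the text does not say whether it is interim or long-term.

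**Working it through.** No formula applies and the article gives no figure to reproduce. The check is a reading of the handling text, in order, against the stated use.

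**1. Which specimen does the additive sentence govern?** The order is serum, plasma, additive step, PBMC. The additive sentence names no specimen; it refers back to each sample. The last specimen named is plasma. PBMC are introduced only afterwards, with their own container and their own freezing medium. On the plain reading the step applies to plasma. Taken more broadly, it would also reach serum, named two sentences earlier.

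**2. Does that fit the stated use?** The abstract's Methods lists serum and plasma among the materials obtained for multiomics analysis. The Discussion describes multiomics as running through proteomic analysis to metabolic profiling. Added protein-containing material and solvent change what such assays measure. This holds whether the garbled term for the human-derived component means a serum or an antibody, so the garbling need not be resolved to see the conflict.

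**3. What if the step was meant for PBMC?** The sentence is then in the wrong place. Plasma is left with a tube and a time limit but no storage temperature, because its −20 °C comes from that same sentence. Under either reading the text needs correction.

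**4. Temperatures side by side.**

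| Specimen | Storage temperature stated | Place stated |
|---|---|---|
| DNA | −70 to −80 °C | main center |
| RNA | −70 to −80 °C | main center |
| Serum | −20 °C | collection sites |
| Plasma | −20 °C (from the additive sentence) | not stated separately |
| PBMC | −20 °C | not stated separately |

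The gap is 50 to 60 °C (−20 − (−70) = 50; −20 − (−80) = 60). All biospecimens are then divided between two central repositories, so a move is described for every type. What is unclear is the temperature after it for serum, plasma and PBMC.

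**5. How many specimens?** The instruction is general, so it covers the plasma of every enrolled patient, up to 100. The number of aliquots cannot be derived, because the same section also plans further biospecimen collection at follow-up and gives no count.

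**The case against.** The strongest reply is that this is a drafting slip. Cell preparation tubes are mentioned just before the additive step, the additives are those used for cells, and the next sentence gives PBMC a freezing medium. The laboratory may well have treated only the cells. That is plausible, and it limits the conclusion: the article shows a wrong instruction, not contaminated plasma.

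A second reply is that a journal article condenses a laboratory manual. This stands for additive ratios, site holding times, per-aliquot time logs and the full storage schedule; their absence is no finding. It does not cover the additive sentence, which is stated and not omitted. Patient follow-up says a guideline to standardize blood samples is still to be developed and that the second and third years use the same protocol. The article therefore does not point to an existing document that overrides the sentence, although it does allow for revision after each year's data.

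A third reply is that no assay is assigned to the plasma aliquots and that multiomics methods are deferred to a later paper. That is correct, and it means the harm is to intended uses described in general terms. It does not justify the additive.

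A reader might go further in three ways that the documents do not support:

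- **That specimens will be degraded, or PBMC made useless.** The article gives no stability data, no time at −20 °C and no described assay on PBMC. Degradation is a risk here, not a certainty.
- **That specimens sit at −20 °C for the whole enrolment period, 2018 to 2021.** The transfer to two repositories contradicts any such assumption.
- **That plasma is diluted by a known fraction, or mixed with another donor's serum.** No ratio is given, and the term used is garbled, so neither can be asserted.

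**Conclusion.** The point holds for the additive step. The Methods, followed as written, put cell-freezing additives into plasma intended for multiomics work, and the text must be corrected even if the step was meant for PBMC. The instruction reaches the plasma of up to 100 patients; its effect on any assay cannot be quantified from the article. Whether any stored plasma was actually treated is unknown and has to be checked.

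The storage temperature is a secondary point. The contrast between −20 °C and −70 to −80 °C is in the text, but the article leaves open whether −20 °C is only interim. It warrants a clarifying statement and does not show that specimens are being lost.

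The conclusion assumes that the additive sentence refers to the specimen named just before it, and that plasma is among the material for the protein and metabolite work described in the Discussion and Conclusion.

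**What to change.** 1. Rewrite the sentence so that plasma and serum are aliquoted neat, with no serum product, DMSO or freezing medium, and cryoprotectant is used only for the PBMC tube. Correct the garbled name of the human-derived component there.
2. Ask each of the 17 centers what was done. Flag any stored plasma that received the additive, so that it is not used unknowingly in proteomic or metabolic assays. If the step was only ever applied to PBMC, nothing needs flagging.
3. State that −20 °C is interim storage at the sites, and that serum, plasma and PBMC are held at the two repositories at the −70 to −80 °C already used for DNA and RNA, or colder for PBMC.

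The cost is a revised procedure sent to the sites, frozen transport and freezer space for three more specimen types, and possibly some flagged aliquots. No patients or visits are added. The first change alone is nearly free.

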### Patient follow-up

All patients will be followed up twice or more per year, with an expected 80% follow-up rate. During the second and third year, patient registry and data collection will be continued using the same protocol. To maintain the credibility of collected data, the steering committee will continuously monitor and audit the collected data. The protocol may be further crafted after evaluating the previous year’s data. Effective data management strategies, including a guideline to standardize body measurements and blood samples, will be developed. Ten patient samples will be selected for next generation sequencing and will be utilized to discover novel genetic mutations.

### Genetic mutation analysis across three-pedigrees for HPAH patients

To determine patients with HPAH, a familial genetic study will be performed. A three-generation pedigree for each PAH patient with or without the existence of *BMPR2, ACVRL1, ENG, CAV1, SMAD1, SMAD4, SMAD9, KCNK3,* and/or *EIF2AK4* mutations will be evaluated. Blood samples from family members of patients with a HPAH will be collected for genetic screening.

### Statistical analysis

Continuous normally-distributed data will be expressed as the means ± standard deviations. Student’s t-tests or one-way ANOVA tests will be used to compare inter-group differences for normally distributed variables. Categorical variables will be analyzed using Pearson’s χ^2^ test or Fisher’s exact test. For all analyses, a two-sided *p* < 0.05 will be considered statistically significant. For longitudinal data comparisons, we will use the Mantel-Cox method to calculate hazard ratios and 95% CIs and the log-rank test to calculate corresponding *p* values. Data analysis will be performed using IBM SPSS Statistics (IBM Corp. Released 2014. IBM SPSS Statistics for Windows, Version 20.0. Armonk, NY: IBM Corp.). Due to the small patient population and seldom references for sample size calculation, the current project will be enrolling 100 consecutive PAH patients initially. Sample size expansion will be done in subsequent studies.

